## Abstract

**Background:**

The cannabis extract nabiximols (Sativex®) effectively supresses withdrawal symptoms and cravings in treatment resistant cannabis dependent individuals, who have high relapse rates following conventional withdrawal treatments. This study examines the efficacy, safety and cost-effectiveness of longer-term nabiximols treatment for outpatient cannabis dependent patients who have not responded to previous conventional treatment approaches.

**Methods/Design:**

A phase III multi-site outpatient, randomised, double-blinded, placebo controlled parallel design, comparing a 12-week course of nabiximols to placebo, with follow up at 24 weeks after enrolment.

Four specialist drug and alcohol outpatient clinics in New South Wales, Australia.

One hundred forty-two treatment seeking cannabis dependent adults, with no significant medical, psychiatric or other substance use disorders.

Nabiximols is an oromucosal spray prescribed on a flexible dose regimen to a maximum daily dose of 32 sprays; 8 sprays (total 21.6 mg tetrahydrocannabinol (THC) and 20 mg cannabidiol (CBD)) four times a day, or matching placebo, dispensed weekly. All participants will receive six-sessions of individual cognitive behavioural therapy (CBT) and weekly clinical reviews.

Primary endpoints are use of non-prescribed cannabis (self-reported cannabis use days, urine toxicology), safety measures (adverse events and abuse liability), and cost effectiveness (incremental cost effectiveness in achieving additional Quality Adjusted Life Years). Secondary outcomes include, improvement in physical and mental health parameters, substance use other than cannabis, cognitive functioning and patient satisfaction measures.

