### Study objectives

This study examines the efficacy, safety and cost-effectiveness of nabiximols in the outpatient treatment of cannabis dependent treatment seeking patients who have not previously responded to conventional psychosocial interventions. Specific study objectives are:Primary Objective 1: To examine the effects of nabiximols vs. placebo on a range of cannabis treatment efficacy outcomes, primarily, changes in illicit cannabis use during treatment and effects on retention in treatment.Primary Objective 2: To examine the adverse event profile and abuse liability of nabiximols as a take home treatment for cannabis use disorder.Primary Objective 3: To assess the costs and health related quality of life (HRQoL) associated with nabiximols treatment and the potential societal savings (decreased health care, improved productivity, and decreased criminal behaviours).Secondary objectives: To examine changes in health related outcomes during outpatient treatment with nabiximols, including a range of mental and physical health dimensions, cognitive function, and psychosocial functioning.

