### Participants

#### Sample size

Based on the primary outcome measure (efficacy, safety and cost-effectiveness of nabiximols in outpatient treatment of cannabis dependence), a total sample size of 142 participants (71 per group) is required to achieve around 22% abstinence rates at 12-weeks for the placebo group (ascertained by average of previous drug administered clinical trials) and approximately 44% abstinence rates for the nabiximols group (based on clinical judgement of double the rate of abstinence than placebo) with 80% power (two-tailed) and α = 0.05.

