	Rey Auditory Verbal Learning Task [62]	Retention of a 15 item word list presented on 5 occasions. Number of words recalled on each presentation, following presentation of a novel list of 15 words; and then after brief and long delays recorded. Recognition of target stimuli also assessed.	Research Interview: Weeks 0, 4, 24

#### Objective 1

To examine cannabis treatment efficacy outcomes, including changes in illicit cannabis use during treatment and treatment retention.Illicit cannabis use is quantified as self-reported number of days of illicit cannabis use and average daily amount of cannabis use in grams at the 4 weekly research interviews using modified Timeline Followback [40] techniques. The primary end-point is self-reported illicit cannabis use days during the maintenance phase of treatment (weeks 1-12). Objective measures of illicit cannabis use will be determined from weekly urine collection with quantitative analysis of urinary THC, THC-COOH, CBD and other cannabinoids. 4-weekly point prevalence abstinence during maintenance phase (weeks 1-4, 5-8, 9-12), and post-treatment period (week 24) will be ascertained by combining self-report data from researcher interviews and urinalysis.Treatment retention (days in protocol treatment) are recorded from clinical records. Participants who do not attend for more than two consecutive weeks are deemed to have dropped out of treatment, and the last scheduled day of dosing is calculated as the end of treatment date.

#### Objective 2

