To assess the costs and health related quality of life (HRQoL) associated with the provision of nabiximols for treatment of resistant cannabis use disorder and the potential societal savings (decreased health care, improved productivity, and changes in criminal behaviors).Cost effectiveness: Consistent with other drug treatment cost effectiveness evaluations [43–45], the primary outcome is Quality Adjusted Life Years (QALY) measured by the SF-6D [46], (at 4 weekly research interviews) determined using area under the curve analysis [47] for each individual. Resources included are all clinical services provided as trial interventions (see Treatment Process Measures below), adverse event management, self-reported health care utilization outside of the trial (hospital, emergency department, primary care and other specialist health services) as well as self-reported participation in criminal activity that will be costed using unit costs (CPI adjusted if necessary) [48]. Lost productivity and personal costs are collected by structured self-report (WHO Health and Performance Questionnaire: Clinical Trials Version) [49]. The costs will be summed and combined with the outcome measure, and the incremental cost-effectiveness ratio [ICER = (C_Nabiximols_-C_Control_)/(E_Nabiximols_-E_Control_)] calculated.

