## Statistical analyses

Chi square and ANOVA tests will be performed to identify any baseline covariates that differ between groups. Prior to carrying out primary and secondary analysis, the percentage of missing values in the raw dataset and Little’s MCAR test will be used to determine if multiple imputation of missing values is required (except for missing urine where cannabis use will be assumed to have taken place). The multiple imputation will be done if the percentage of missing values exceeds 5%.

All analyses will use Intention-to-treat, which is defined as any person who is randomised to one of the study arms and receives at least one dose of study medications. Mixed Models for Repeated Measures (MMRM) will compare groups on changes in outcome variables (cannabis use and secondary outcomes) in the medication phase with the multiply imputed dataset, (assuming that Little’s MCAR at Random test confirms the data to be missing at random). In addition, we will perform a sensitivity analysis based on only those with complete data, and compare results to that from the MI dataset analysis.

Adverse Events will be analysed using chi-square. A Cox proportional hazards model will compare retention in treatment between study arms, controlling for potential confounds. The impact of the intervention on post-medication outcomes will compare changes in cannabis use outcomes at baseline and at follow up between groups using MMRMs.

Family-wise error corrections will control for Type 1 errors where multiple comparisons are performed within a particular analysis where post hoc contrasts are performed to further explore interesting (significant) findings.

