## Study limitations

This study has a number of possible limitations. One issue relates to retention in study protocol. Participation in the study is voluntary, and study procedures span 24 weeks, including 13 weeks of study treatment interventions. The lengthy treatment duration in the study is generally longer than conventional treatment of cannabis dependence, and participants may be deterred from entering the trial or prematurely terminate study participation, which in turn may have implications in assessing effectiveness of treatment outcomes and research follow-up. Similarly, individuals enrolling in a medication study may have different levels of interest or commitment to the CBT in the study, which may enhance heterogeneity of outcomes.

The study uses a flexible dosing approach to medication. Whilst a fixed regimen – or indeed a structured comparison of different doses (e.g. high or low) is often used in many medication studies – experience from opioid agonist clinical and research practice highlights the need to tailor doses to individual requirements, reflecting differing physiological tolerance, adverse event profiles and behavioural characteristics of patients. Nevertheless, the different doses used may increase heterogeneity of outcomes and limit the ability to detect significant differences if there is indeed a major dose effect.

Measures of illicit cannabis use during treatment are the primary study outcome, with self-reported use (via the TLFB) as the primary endpoint. Participants may have a response bias and report inaccurate drug use to both clinicians and researchers. Whilst objective assessment of illicit cannabis use using urine drug screening should enhance self-report validity, it remains to be seen whether illicit cannabis use can be differentiated from prescribed nabiximols use. Various toxicological approaches are being examined to validate the identification of illicit cannabis use in nabiximols prescribed patients (to be described elsewhere).

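### The Abstract and the sample-size section conflict with the Objective 1 text and the limitations section on the primary endpoint, and the stated family-wise rule would not cover the Abstract's list

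*Protocol article*

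**What the plan says.** The protocol article describes what is primary in several places.

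- Abstract, Methods/Design (plural): "Primary endpoints are use of non-prescribed cannabis (self-reported cannabis use days, urine toxicology), safety measures (adverse events and abuse liability), and cost effectiveness".
- Study objectives, Primary Objective 1: "primarily, changes in illicit cannabis use during treatment and effects on retention in treatment". Retention is not in the Abstract's list of primary endpoints.
- Sample size (singular): "Based on the primary outcome measure (efficacy, safety and cost-effectiveness of nabiximols in outpatient treatment of cannabis dependence". The calculation that follows uses abstinence at 12 weeks, 22% on placebo and 44% on nabiximols, with 142 participants, 80% power and a two-tailed alpha of 0.05.
- Outcome and treatment process measures, Objective 1 (singular): "The primary end-point is self-reported illicit cannabis use days during the maintenance phase of treatment (weeks 1-12". Four-weekly point prevalence abstinence, from self-report and urinalysis combined, is described there as a separate measure.
- The same section, Objective 3, for the economic evaluation: "the primary outcome is Quality Adjusted Life Years (QALY) measured by the SF-6D".
- Study limitations (singular): "Measures of illicit cannabis use during treatment are the primary study outcome, with self-reported use (via the TLFB) as the primary endpoint".

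The multiplicity rule is in Statistical analyses: "Family-wise error corrections will control for Type 1 errors where multiple comparisons are performed within a particular analysis where post hoc contrasts are performed". Its purpose is given as "to further explore interesting (significant) findings".

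**The concern.** A reader cannot tell from the article which test carries the two-sided 0.05. The Abstract puts urine toxicology beside self-reported days. The Sample size section powers the trial on a proportion abstinent. Objective 1 and Study limitations give the role to self-reported use alone.

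The choice could change the answer. Days, urine and abstinence handle missing data and measurement differently: a missing urine is counted as use, while other missing values may be multiply imputed. Study limitations also concedes that urine testing may not separate illicit cannabis from the prescribed product. A result on one measure therefore need not be matched on another, and the present text would let either days or urine be cited as a primary endpoint.

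The one family-wise statement does not settle this. It corrects comparisons inside an analysis and says nothing about several primary endpoints analysed separately.

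There is also a consequence for power. The stated 80% belongs to a binary outcome that no section names as the primary endpoint.

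**Working it through.** **1. Reproduce the plan's own figure.** Inputs from Sample size: p1 = 0.22, p2 = 0.44, two-sided alpha 0.05, power 80%. Allocation is 1:1 (Randomisation and blinding). With pooled variance under the null and no continuity correction:

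n per arm = [1.960 × √(2 × 0.33 × 0.67) + 0.842 × √(0.22 × 0.78 + 0.44 × 0.56)]² / 0.22²

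= [1.960 × 0.6650 + 0.842 × 0.6465]² / 0.0484 = (1.303 + 0.544)² / 0.0484 = 3.413 / 0.0484 ≈ 70.5, rounded up to 71.

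The total is 142, an exact match, and power at 71 per arm is 80.3%. So the sample size is that of one comparison of abstinence proportions at the full 0.05. No alpha was set aside for a second primary test.

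**2. Set the sections side by side.**

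| Section | What it treats as primary |
|---|---|
| Abstract | Days, urine, adverse events, abuse liability, cost effectiveness |
| Sample size | A three-domain phrase, sized on 12-week abstinence |
| Objective 1 text | Self-reported use days, weeks 1-12 |
| Study limitations | Self-reported use |

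The last two agree. The first two differ from them and from each other.

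**3. What the family-wise rule would leave open.** Take the two cannabis-use measures that the Abstract calls primary, days and urine. Assume, because the document does not say so, that each is tested at 0.05 and that either could be claimed as success. With no true effect:

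- Independent tests: 1 − 0.95² = 0.0975, or 9.8%.
- Correlated test statistics (bivariate normal, one million simulated draws per setting, correlation assumed): 9.5% at 0.3, 9.0% at 0.5, 7.8% at 0.8.

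Days and urine reflect the same behaviour in the same people, so a positive correlation is more plausible than independence. The document gives no value for it.

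**4. The reading under Objective 1 and Study limitations.** One confirmatory endpoint tested once at two-sided 0.05 gives a confirmatory error of 5%.

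**5. Power for the named endpoint.** Use days are a count over the treatment period. Cannabis use is to be analysed with a mixed model for repeated measures, not by comparing two proportions. The document gives no mean difference or standard deviation for use days, so neither the power nor the required sample size for that endpoint can be computed from it.

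**The case against.** The strongest reply is that the plan does name a single primary endpoint. The Objective 1 text does so explicitly and Study limitations repeats it. The Abstract's list can be read as a summary of the three primary objectives (efficacy, safety, cost) with their measures in brackets. Study limitations presents urine as support for the validity of self-report, not as a rival claim. A fuller hierarchy may sit in a statistical analysis plan that is not shown.

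Much of this stands. A reader might infer from the Abstract and the narrow family-wise rule that confirmatory type I error is uncontrolled. The documents do not support that: two sections point to one endpoint and hence 5%, and no section says that success on any one of several endpoints is enough.

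A reader might also count four efficacy measures (days, urine, abstinence, retention) and get 18.5%, or the Abstract's five items and get 22.6%. Neither figure describes an efficacy error rate for this plan. No section labels abstinence or retention a primary endpoint. Adverse events and abuse liability serve a separate objective. The cost-effectiveness ratio is to be calculated, and no 0.05 test of it is described.

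Nor is it an error that the rule corrects contrasts that follow a significant result. That is a recognised approach, and it plausibly covers period-by-period contrasts within one model. The exact model contrast and any ordering of secondary outcomes are ordinary analysis-plan content.

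The contradiction itself remains. The Sample size section is body text, not an abstract. It describes the primary outcome measure as three domains and then uses abstinence. An unseen analysis plan cannot make the published statements agree.

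**Conclusion.** The concern holds as a conflict between stated passages. The Abstract and Sample size section disagree with the Objective 1 text and Study limitations about the primary endpoint, and the family-wise rule would not protect the Abstract's list if it were tested as written.

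For days and urine together the error would be between about 7.8% (assumed correlation 0.8) and 9.8% (independence), conditional on an either-one-wins rule that the document does not state. It is 5% if the Objective 1 text governs. The finding is therefore ambiguity about which test is confirmatory, not a demonstrated loss of type I error control.

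One part needs no such assumption: the 80% power was derived for 12-week abstinence and cannot be read as the power for self-reported use days.

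**What to change.** Before unblinding:

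1. State that self-reported illicit cannabis use days over weeks 1-12 is the sole confirmatory efficacy endpoint, tested at two-sided 0.05.
2. Conform the Abstract and the Sample size section to this. Label urine toxicology, abstinence and retention as secondary efficacy outcomes. Present safety and cost effectiveness as separate objectives that carry no efficacy claim.
3. In Sample size, say that the 80% power applies to 12-week abstinence and not to the primary endpoint. Add a power justification for use days, with the assumed difference and standard deviation and their source.

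With one confirmatory test, alpha stays at 0.05 and multiplicity adds nothing to the sample size. There are two costs. The secondary efficacy outcomes lose any stand-alone confirmatory claim. The third step is more than rewording, because it needs inputs that the document does not contain, and the resulting power at 71 per arm may be higher or lower than 80%.

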**Discussion:**

This is the first outpatient community-based randomised controlled study of nabiximols as an agonist replacement medication for treating cannabis dependence, targeting individuals who have not previously responded to conventional treatment approaches. The study and treatment design is modelled upon an earlier study with this population and more generally on other agonist replacement treatments (e.g. nicotine, opioids).

**Trial registration:**

Australian and New Zealand Clinical Trial Registry: ACTRN12616000103460 (Registered 1st February 2016).

**Electronic supplementary material:**

The online version of this article (10.1186/s12888-018-1682-2) contains supplementary material, which is available to authorized users.

## Background

Approximately 183 million people aged 15-64 years, (3.8%) of the global population currently use cannabis worldwide, dwarfing the use of all other globally regulated substances [1, 2] . In Australia, it is estimated that about 6.6 million people aged 14 years or older have used cannabis at some stage in their lives [3], compared with approximately 22.2 million in the USA [4, 5]. Close to 10.4% of adults in Australia between the age of 14 and over have used cannabis in the past 12 months [6], of which approximately 10% report dependent patterns of use, making it the most common illicit drug of dependence [7].

Cannabis dependence is associated with a range of health problems including cognitive, psychiatric, cardiovascular and respiratory disorders [1, 7, 8], and considerable societal burden [9]. Cannabis ranks second of all illicit drugs in hospital associated costs [10], is the primary drug of concern in 24% of Australian alcohol and other drug treatment services (AODTS) [11], and is identified as a problem drug for 55% of addiction-related treatment episodes [11].

The effectiveness of existing treatments for cannabis use disorders is far from satisfactory but consistent with many other addictive disorders. Reviews of current ‘best practice’ psychosocial interventions (e.g. cognitive behavioural therapy (CBT)) indicate that around 80% of patients relapse within 1-6 months [12]. Treatment of acute cannabis withdrawal is associated with similar relapse rates [13, 14]. More effective approaches are required for people seeking treatment for cannabis use related problems, and as with the treatment of other chronic addiction conditions, there is particular interest in the development of treatment approaches that combine medication with psychosocial interventions [15]. Whilst the importance of medication to support current best practice psychosocial interventions has been identified [15], there are as yet no efficacious pharmacotherapies for cannabis dependence [16]. Medication trials for cannabis dependence are an emerging area of research [17]. Most trials have either been laboratory based or focused only on treating withdrawal symptoms during initial abstinence rather than longer term relapse prevention [18]. Medicines tested for withdrawal treatment – with limited efficacy include antidepressants such as bupropion, [19] the mood stabilizers divalproex [20] and lithium [14], the α_2−_adrenergic agonist lofexidine [21] and the supplement N-acetylcysteine (NAC) [22].

A promising alternative is agonist replacement (or substitution) cannabinoid pharmacotherapies, akin to opioid or nicotine replacement treatment [23]. Studies of cannabinoid agonist medications in withdrawal treatment indicate successful amelioration of withdrawal symptoms. The rationale for agonist medications in cannabis dependence is that they provide a safer route of administration (than smoking), should reduce unsanctioned drug use by preventing withdrawal and reducing cravings [13], and attenuate the acute effects of smoked cannabis [24, 25], potentially facilitating greater engagement in psychosocial interventions. Together, these anticipated effects should provide those also receiving psycho-social interventions and related support to make the necessary lifestyle changes, and distance themselves from drug-related cues, prior to tapering off agonist medication.

Dronabinol, an orally administered synthetic analogue of THC, dose-dependently reduced withdrawal symptoms in the laboratory [20], and improved retention in an outpatient setting [26, 27]. Nabilone, another synthetic THC analogue was efficacious in laboratory experiments, but is as yet untested in clinical settings [21]. A double blind placebo-controlled RCT [13] of nabiximols, an oromucosal spray with approximately equal parts of the cannabinoids THC and CBD, demonstrated successful suppression of withdrawal symptoms and cravings during inpatient detoxification, with greater rates of treatment completion than placebo. However, the high rates of relapse from continuous abstinence following discharge (over two thirds in both groups, but delayed in the nabiximols group) indicate limited longer-term benefits of a 6-day nabiximols regimen.

The high rate of relapse after acute medication-assisted withdrawal highlights the need for longer-term outpatient trials of cannabinoid replacement therapies [15, 16].

Only one RCT has examined longer-term cannabinoid agonist replacement treatment. Levin and colleagues [28], compared a 12-week outpatient course of dronabinol to placebo in 121 cannabis dependent treatment seekers. Although dronabinol was well tolerated, had higher treatment retention and reduced withdrawal symptoms, there was no advantage of dronabinol over placebo in achieving abstinence from illicit cannabis, the primary end-point of the study.

The pharmacological profile of nabiximols may have advantages over other available THC agonist medications. Nabiximols is approved in Australia and a number of countries for symptomatic relief of moderate to severe spasticity in multiple sclerosis. It is an oralmucosal spray containing extracts from *Cannabis sativa* plants grown under licence in the UK by the company GW Pharmaceuticals, containing 2.7 mg THC and 2.5 mg CBD per 0.1 ml spray, with small amounts (4 mg/ml) of other plant-derived cannabinoids. The buccal route of administration provides a rapid onset of action and more favourable pharmacokinetics than oral THC or dronabinol [26], more closely mimicking smoked cannabis use. The anxiolytic effects of CBD present in nabiximols may also ameliorate cravings and anxiety associated with dependent cannabis use and withdrawal.

Two outpatient pilot studies have examined the potential role of nabiximols as an agonist replacement therapy for cannabis withdrawal [29, 30]. In a within-subject placebo controlled randomised controlled trial with 8 participants, high nabiximols doses (up to 108 mg THC/100 mg CBD daily) were well tolerated and significantly reduced cannabis withdrawal symptoms in those achieving abstinence from illicit cannabis use [29]. The same research group have recently reported positive clinical findings (78% abstinence) in an open label 12 week course of treatment with nabiximols (average daily dosage 77.5 mg THC/ 71.7 mg CBD) and psychological treatment in four participants [30]. These studies highlight nabiximols potential as a longer term agonist replacement approach, however, to date, no outpatient large scale randomised controlled trial has examined the safety and efficacy of nabiximols as a substitution medication in the management of cannabis dependence.

